### Study Population and Sample Size

The trial will include 130 adults aged 18 to 60 years with opioid use disorder who are already receiving buprenorphine treatment, with no criteria regarding gender identity, race, or ethnicity.

Inclusion criteria are having the ability to provide informed consent, age 18 to 60 years, having adequate English proficiency, being within the first 120 days of starting buprenorphine, receiving buprenorphine pharmacotherapy under the care of a licensed health care provider and being willing to provide the name of the provider or practice, being capable of using common software apps on a smartphone, and having access to an internet-enabled smartphone that meets minimal operating system requirements for the duration of the study. Exclusion criteria are having a history of reSET-O use, having participated in user-testing of PEAR-008 or any investigational drug trials within 30 days of trial enrollment, or currently receiving methadone or naltrexone pharmacotherapy.

The sample size and power were based on the primary engagement outcome, determined by frequency of interaction with the intervention, percentage of module completion, and approval ratings. A sample size of 130, α=.05, and power=0.80 will allow for detection of a moderate effect size (*d*=0.50).

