### Randomization and Blinding

Following informed consent, the baseline assessment and confirmation of eligibility, participants will be randomly assigned to 1 of 2 treatment groups: reSET-O or PEAR-008. Randomization lists will be prepared by the study sponsor (Pear Therapeutics) prior to the start of the study. Randomization will be 1:1 and stratified by site and gender with a block size of 10. An electronic list of IDs, access codes, and credentials will be securely provided to the sites. There will be no blinding; this is an open-label study.

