#### PEAR-008

PEAR-008 is an investigational device with therapeutic content and a contingency management reward system that are similar to those in reSET-O; however, clinical content enhancements have been made, and the therapy has been reformatted as a game with mechanics designed to promote engagement. Content enhancements include use of person-centered language and lowering the reading level to make it more accessible. In PEAR-008, the reSET-O therapy lessons were divided into a tiered structure of shorter chapters with the intent of providing small, achievable goals to help keep users motivated and engaged. Each chapter has an associated quiz based on the fluency training approach.

The PEAR-008 home screen shows a nature scene that transitions from winter to summer as the patient progresses through therapy (Figure 1). The game economy of PEAR-008 is variable, consisting of the ability to earn stars that unlock virtual rewards such as birds and home-screen upgrades, as well as Mystery Boxes. The Mystery Boxes replace the contingency management rewards wheel in reSET-O and contain either virtual (stars) or tangible rewards (gift card with value ranges from $5 to $100) with the same odds of winning a tangible reward at each level of value as those in reSET-O. Similar to reSET-O users, PEAR-008 users earn the opportunity for contingency management rewards by completing fluency training quizzes (ie, therapy lessons). Engagement is also incentivized: a user can earn rewards by repeating a chapter and by engaging at least once daily with PEAR-008. The user is required to complete a daily check-in the first time they open the app each day. The check-in consists of a series of questions related to substance use, medication use, general recovery status, and recovery-specific questions regarding cravings, triggers, and problems the user is managing.

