### Study Procedures

#### Overview

All study visits will be conducted remotely. Each prospective participant will complete a short screening assessment, and if basic eligibility is confirmed, complete informed consent procedures and sign an electronic informed consent form prior to completing the baseline assessment. After baseline assessments, participants will be randomly assigned to either reSET-O or PEAR-008 groups. Study staff will assist each participant with installation of their assigned digital therapeutic on their mobile device. Staff will provide training on the app’s use. Study participants will be enrolled for 12 weeks, with weekly virtual sessions during weeks 1-8 and a final visit at week 12, to evaluate the impact of reSET-O and PEAR-008 on participant engagement and treatment outcomes. Participants will also complete slightly longer assessments at weeks 4 and 8.

Weekly study assessments completed during the first 8 weeks of treatment include saliva drug screening (participants will receive drug screening equipment on a regular basis by mail; urine drug screen results may be retrieved from the electronic medical record for AREF participants), timeline followback [29], and adverse event reporting. Additional self-report assessments will be delivered at week 4 and week 8.

Participants will attend a virtual end of treatment study session at 12 weeks to complete the following: saliva drug screening, timeline followback, and adverse event reporting assessment. Additional measures will be assessed at the 12-week follow-up visit (Table 1).

**Table 1 table1:** Study objectives and endpoints.

Objective			Endpoint

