**Secondary**			
	To evaluate the impact of PEAR-008 compared to reSET-O on treatment retention	Time to dropout (last contact with a participant)	
	To evaluate the impact of PEAR-008 compared to reSET-O on abstinence from illicit opioids	Abstinence will be defined as abstinence on patient self-reports (via timeline followback) and the absence of nonbuprenorphine opioids on saliva drug screens. Abstinence (binary outcome: yes or no) will be determined 9 times, weekly during weeks 1-8 and at week 12.	
	To evaluate participants’ digital therapeutic use patterns of PEAR-008 compared to reSET-O	Session duration; number of lessons and chapters completed; number of completed self-report assessments; response to notifications	
	To evaluate the impact of PEAR-008 compared to reSET-O on change in psychiatric symptom severity between baseline and follow-up	Depression symptoms with Patient Health Questionnaire–8; Anxiety symptoms with Generalized Anxiety Disorder–7	
	To evaluate the impact of PEAR-008 compared to reSET-O on change in recovery capital and resilience between baseline and follow-up	Brief Assessment of Recovery Capital–10; Connor-Davidson Resilience Scale–10	
	To evaluate participant motivation and satisfaction over time with PEAR-008 compared to reSET-O	Participant surveys administered at baseline, week 4, week 8, and week 12; participant interview at follow-up	
	To evaluate a more global measure of engagement by combining data from secondary endpoints 3-6	A multivariate analysis of variance combining data from secondary endpoints 3-6	

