#### Participant Motivation and Satisfaction

Participant motivation and satisfaction will be evaluated via surveys and qualitative interviews. Surveys will be administered at baseline, week 4, week 8, and week 12, with a range of questions designed to evaluate participant motivation (baseline only) and satisfaction with their assigned intervention (eg, ease of use, relevance, satisfaction).

A subset of participants (approximately 10 per treatment arm) will be asked to participate in a 1-on-1 qualitative interview to evaluate their respective experiences with each therapeutic, particularly ease of use and acceptability. Interviews will last approximately 60 minutes, be conducted by study staff, and will be performed remotely via video or phone. Interview transcripts will be coded and analyzed using grounded theory methodology to identify key themes. An inductive, open coding approach will be used to assign emerging categories. Emerging categories will be grouped to arrive at high-level themes during axial coding, and their properties and dimensions will be identified and described in a codebook.

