#### Secondary Endpoint Analysis

Abstinence will be self-reported by patients via timeline followback and assessed as the absence of opioids (except buprenorphine) on saliva drug screens. Data on abstinence (binary yes and no) will be evaluated with the 9 possible saliva drug screens and urine drug screen and timeline followback data at weeks 1-8 and week 12. Differences between the treatment arms in abstinence will be assessed with a generalized estimating equation analysis using the binomial abstinence outcome as the dependent variable, assessment time, treatment, and the interaction between assessment time and treatment as fixed effects and subject as a random factor. This generalized estimating equation will be compared to a second generalized estimating equation without a treatment term using a likelihood ratio test to evaluate the impact of treatment. A treatment responder analysis will also be conducted, with a treatment responder defined as someone with ≥80% of all saliva drug screens and urine drug screens and timeline followback reports negative for all nonprescribed opioids over the course of the trial.

Treatment retention will be measured as time to dropout (number of days from baseline to last face to face contact) and analyzed using the Kaplan Meier method followed by a log rank test to compare treatment groups.

Patient assessments of recovery capital (Brief Assessment of Recovery Capital–10) resilience (Connor-Davidson Resilience Scale–10) and severity of co-occurring psychiatric symptoms (Patient Health Questionnaire–8 and Generalized Anxiety Disorder Questionnaire–7) will be evaluated with a repeated measures mixed model in a manner consistent with the primary endpoint.

Participants’ use patterns with PEAR-008 and reSET-O will include total time engaged, number of lessons and chapters completed, number of lessons and chapters repeated, number of completed self-report assessments, and response to notifications. Descriptive statistics of each treatment arm will be summarized and differences between PEAR-008 and reSET-O will be assessed with a *t* test (or its nonparametric alternative if the distributional assumptions are violated).

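### Secondary use-pattern tests compare raw counts whose units and schedules differ by arm, and by row order the engagement MANOVA includes clinical scales

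*Protocol article*

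**What the plan says.** Besides total time engaged, Secondary Endpoint Analysis lists these use measures: "number of lessons and chapters completed, number of lessons and chapters repeated, number of completed self-report assessments, and response to notifications". It then says that "differences between PEAR-008 and reSET-O will be assessed with a" t test, or a nonparametric alternative if its assumptions fail. It gives no conversion between lessons and chapters and no denominator for self-reports.

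The intervention sections describe how the arms differ:

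- **Content.** reSET-O has 67 lessons. For PEAR-008, "the reSET-O therapy lessons were divided into a tiered structure of shorter chapters".
- **Self-reports.** PEAR-008 requires a check-in at the first opening of the app each day. reSET-O prompts every 72 hours and also lets the user report at any time.
- **Repeats.** Rewards for repeating a chapter are described for PEAR-008. The reSET-O section mentions rewards for completing lessons only.

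The last secondary row of Table 1 is a MANOVA, with the aim "To evaluate a more global measure of engagement by combining data from secondary endpoints 3-6". The rows are not numbered.

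**The concern.** A between-arm test on a count is informative only if one unit means the same in both arms. If a lesson is cut into several chapters, two participants who cover the same material record different counts. The Primary Endpoint Analysis section recognises this: it justifies active sessions as the primary measure because chapters are brief and lessons longer. The secondary analysis then tests the very counts that this reasoning set aside. The number of completed self-reports raises a similar problem, because the apps ask at different intervals.

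The MANOVA raises a separate question of labelling. If it includes symptom and resilience scales, a difference in depression scores alone could make it significant, and the result would be reported under the name of engagement.

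At stake is whether a difference in packaging, prompting schedule or symptoms is presented as greater engagement with PEAR-008, which is the direction the trial hypothesises.

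**Working it through.** **The plan's own figure.** Study Population and Sample Size says: "A sample size of 130, α=.05, and power=0.80 will allow for detection of a moderate effect size" (d = 0.50). A two-sided two-sample t test needs 63.8, so 64 per arm or 128 in total; with 65 per arm the power is 0.808. The stated 130 reproduces. (Sidedness is not stated; a one-sided test would need 100.) This figure is not in dispute. It supplies the arm size: "Randomization will be 1:1 and stratified by site and gender with a block size of 10" gives 130 / 2 = 65 per arm.

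**Self-report schedule.** "Study participants will be enrolled for 12 weeks", so 12 × 7 = 84 days.

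- PEAR-008: at most one required check-in a day, 84.
- reSET-O: one prompt per 3 days, 84 / 3 = 28.
- Scheduled ratio: 84 / 28 = 3. At 60% completion in both arms the counts are 50.4 and 16.8.

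**Content counts.** Let k be the number of chapters per lesson (not given, so assumed). Someone who completes half the content records 67 × 0.5 = 33.5 lessons in reSET-O. In PEAR-008 the same content is 67 × 0.5 × k chapters: 41.9 at k = 1.25, 50.3 at 1.5, 67 at 2 and 100.5 at 3.

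**Effect on the planned test.** Suppose the share of content completed has the same mean m and SD s in both arms. Then the standardised difference in raw counts is

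d = m(k − 1) / [s √((1 + k²)/2)],

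and power with 65 per arm is about Φ(d√(65/2) − 1.96). For a uniform share, m = 0.5 and s = 0.289:

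- k = 1.25: d = 0.125 / 0.327 = 0.38; power ≈ Φ(2.18 − 1.96) = 0.59.
- k = 1.5: d = 0.25 / 0.368 = 0.68; power ≈ Φ(3.87 − 1.96) = 0.97.
- k = 2: d = 0.5 / 0.456 = 1.10; power ≈ Φ(6.25 − 1.96) > 0.99.

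Simulation of the t test (4,000 trials per cell, 65 per arm, identical engagement in both arms) for three assumed distributions of the share completed gives these rejection rates:

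| Comparison | Beta(1,1) | Beta(0.5,0.5) | Beta(2,2) |
|---|---|---|---|
| Common scale (k = 1) | 4.2% | 5.0% | 4.8% |
| k = 1.25 | 57.8% | 41.8% | 79.2% |
| k = 1.5 | 97.3% | 87.5% | 99.9% |
| k = 2 | 100% | 99.9% | 100% |
| k = 3 | 100% | 100% | 100% |
| Self-reports, 84 v 28 scheduled | 100% | 100% | 100% |

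A rank test does not remove the shift, so the nonparametric alternative does not help.

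**MANOVA content.** Counting the secondary rows of Table 1 in order: 1 retention; 2 abstinence; 3 use patterns; 4 PHQ-8 and GAD-7; 5 recovery capital and resilience; 6 motivation and satisfaction; 7 the MANOVA. On this count, endpoints 3-6 include four clinical or recovery scales. Row 6 also contains a rating that treatment cannot affect: the surveys are intended "to evaluate participant motivation (baseline only) and satisfaction with their assigned intervention", and the baseline assessment precedes randomisation.

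**The case against.** Several counter-arguments have force.

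- **Lessons may persist in PEAR-008.** The content is tiered, and the Figure 1 legend refers to a lessons icon on the home screen. The listed measure could mean lessons in both arms, plus chapters where they exist. The sample size section also mentions a percentage of module completion. This stands as a reason to make the point conditional. It does not settle it, because the analysis text names neither a common unit nor a percentage.
- **The simulation presupposes the shift.** True: it cannot show what k is. It shows only how small a ratio is enough to matter at this sample size.
- **Derivation rules may sit in the SAP.** A chapter-to-lesson map could. What the article does state is a between-arm test on counts, and that needs changing if the counts are raw.
- **Self-report assessments are not defined.** The Overview uses the term for the week 4 and week 8 instruments, which both arms receive on the same schedule; on that reading the 84 v 28 contrast falls away. Listing the item among app use patterns favours the in-app reading. Even then 28 is not a ceiling, since reSET-O users may self-initiate reports, and 84 is reached only if PEAR-008 is opened every day.
- **Rewarded repeats are part of the intervention.** A difference in repeats is therefore partly a treatment effect, though it is not a like-for-like measure of interest in the content.
- **The endpoint numbering is inferred.** Endpoints 3-6 could instead be the four use measures within one Table 1 row. The clinical-scale objection would then fall, but the non-equivalent counts would still enter the MANOVA.

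**Conclusion.** The point holds, conditionally, for the secondary engagement analyses. If chapters are counted against lessons, the counts are biased toward PEAR-008 at equal content completed. With equal engagement the planned t test then rejects about 42-79% of the time at 1.25 chapters per lesson, 88-100% at 1.5 and over 99% at 2 or more. These figures assume 65 per arm, a mean of half the content completed and the three distributions shown; the article gives neither the ratio nor the distribution. The 3:1 self-report ratio is a scheduled ratio, not a forecast, and depends on the in-app reading. By row order, a significant MANOVA need not reflect engagement.

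A reader might go further in four ways that the document does not support:

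- That the tests favour PEAR-008 whatever participants do. Total time engaged and response to notifications do not have the lesson/chapter unit problem, and low enough use of PEAR-008 could cancel or reverse the gap.
- That the MANOVA adds clinical scores to an engagement score. It tests the outcomes jointly; it is not a sum.
- That baseline imbalance would produce a false engagement finding. Nothing says the baseline rating enters the MANOVA, and under randomisation a baseline variable differs only by chance, which alpha covers. Including it would mainly dilute power.
- That dropouts are excluded from the MANOVA. The article says missing data will not be imputed, with sensitivity analyses possible, but states no complete-case rule for this analysis, and app logs can exist for people who miss visits.

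The primary endpoint and the sample size are unaffected.

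**What to change.** 1. **Content.** Analyse the percentage of total therapeutic content completed, or lesson-equivalents, where a PEAR-008 lesson counts once all its chapters are done.
2. **Self-reports.** State whether in-app reports are meant. If so, analyse the percentage of scheduled reports completed, or the percentage of scheduled reporting windows that contain a report. Using the same 28 windows of 72 hours in both arms is the closer match. A user who reports once every three days scores 28/84 = 33% in PEAR-008 but 28/28 = 100% in reSET-O on the first scale, and 100% in both on the second.
3. **Raw counts and repeats.** Report by arm, descriptively, without a test.
4. **MANOVA.** Number the secondary endpoints. Restrict the engagement MANOVA to post-randomisation engagement measures (use patterns on the common scale and satisfaction ratings), leaving out PHQ-8, GAD-7, the recovery capital and resilience scales and the baseline-only interest rating. Otherwise drop it.

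The cost is a chapter-to-lesson map and some wording; existing app data suffice. The downside is that observed differences may look smaller than they would on raw counts.

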**Methods:**

Due to the COVID-19 pandemic, this study was redesigned using a decentralized model because it was not possible to conduct medication initiation and study visits in person, as initially intended. A decentralized, randomized controlled trial design will be utilized to compare patient engagement with PEAR-008 and that with reSET-O using both subjective and objective assessments. The study population will consist of approximately 130 individuals with opioid use disorder (based on Diagnostic and Statistical Manual of Mental Disorders 5 criteria) who have recently started buprenorphine treatment for opioid use disorder. Participants will be virtually recruited and randomly assigned to receive either PEAR-008 or reSET-O. All study sessions will be virtual, and the duration of the study is 12 weeks. The primary outcome measure of engagement is operationalized as the number of active sessions per week with either PEAR-008 or reSET-O. (An active session is any session that contains some active participation in the app, such as navigating to a different screen, engaging with a learning module, or responding to a notification.) Subjective dimensions of engagement will be assessed with participant surveys. The hypothesis is that PEAR-008 will have significantly greater participant engagement than reSET-O.

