## Methods

### Overview

We will compare reSET-O to PEAR-008 and evaluate objective differences in participant engagement with each digital therapeutic. Secondary outcomes include subjective differences in engagement, opioid use disorder treatment outcomes (ie, retention in treatment and abstinence from opioids), symptoms of common comorbid mental health conditions, including anxiety and depression, recovery supports (eg, recovery capital and resilience), and participant satisfaction with their assigned digital therapeutic. Exploratory aims include evaluating development of cognitive behavioral therapy skills and buprenorphine adherence.

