Treatment motivation and satisfaction will be evaluated based on individual participants’ rating of interest in using (baseline only), ease of use, satisfaction, perceived helpfulness, and likelihood of recommending reSET-O or PEAR-008. Descriptive statistics (mean, median, standard deviation) will be performed on Likert scale and multiple choice items that assess user satisfaction and attitudes about the patient mobile app. Analyses will be conducted on data collected at each assessment point throughout the study, ratings over the course of the study, and for overall user satisfaction as measured at the end of the study.

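### Satisfaction over time is a comparative secondary objective, but its stated analysis is descriptive and names no satisfaction-specific between-arm estimate or confidence interval

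*Protocol article*

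**What the plan says.** The secondary rows of Table 1 in the protocol article include this objective: "To evaluate participant motivation and satisfaction over time with PEAR-008 compared to reSET-O". Its endpoint is given as "Participant surveys administered at baseline, week 4, week 8, and week 12; participant interview at follow-up". The Overview under Methods says "Secondary outcomes include subjective differences in engagement" and, later in the same sentence, lists participant satisfaction as a further item. The abstract says "Subjective dimensions of engagement will be assessed with participant surveys".

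The Secondary Endpoint Analysis section describes separate ratings of usability, satisfaction, helpfulness and willingness to recommend, plus an interest rating taken at baseline only. The stated method is: "Descriptive statistics (mean, median, standard deviation) will be performed on Likert scale and multiple choice items that assess user satisfaction". The next sentence reads "Analyses will be conducted on data collected at each assessment point throughout the study, ratings over the course of the study", and then adds overall satisfaction at study end. It says which data are analysed, not how, and it does not mention the arms.

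The last secondary row of Table 1 gives, as a global engagement measure, "A multivariate analysis of variance combining data from secondary endpoints 3-6".

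**The concern.** The objective asks two things: whether satisfaction differs between the products, and how it moves over time. Means, medians and SDs answer neither with a stated uncertainty. Readers would be left to compare raw summaries by eye across several items and three post-baseline visits.

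The article's general rule is not to impute missing data, so each visit's table would describe whoever answered at that visit. That applies to every visit-based outcome here, but a longitudinal model at least uses all of a participant's available ratings together.

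The trial is open-label. With several items and visits and no named contrast, the choice of which comparison to emphasise stays open until the data have been seen. The Introduction gives satisfaction, alongside engagement, as something PEAR-008 was built to improve, so readers will look for this result.

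**Working it through.** **1. What the article states for each secondary endpoint.** Table 1 does not number its rows; the numbers below are the order of the secondary rows.

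| Row | Secondary endpoint | Between-arm method in Secondary Endpoint Analysis |
|---|---|---|
| 1 | Retention | Kaplan-Meier with log-rank test |
| 2 | Opioid abstinence | GEE with treatment and time × treatment (the added responder analysis has no named test) |
| 3 | Use patterns | *t* test or nonparametric alternative |
| 4 | Depression and anxiety scales | Repeated-measures mixed model |
| 5 | Recovery capital and resilience | Repeated-measures mixed model |
| 6 | Motivation and satisfaction | None named; descriptive statistics |
| 7 | Global engagement | MANOVA over 3-6 (named in Table 1 only) |

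The closest parallel is row 3. There the plan gives descriptive statistics by arm and then adds that "differences between PEAR-008 and reSET-O will be assessed with a" *t* test or its alternative. For row 6 the descriptive half is present and the comparative half is not. The exploratory skills questionnaire and medication adherence also receive between-arm models.

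**2. Could another stated analysis supply the contrast?**

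- *MANOVA.* By row count, endpoint 6 is motivation and satisfaction, so satisfaction enters this analysis, presumably with arm as the factor. An omnibus result over use patterns, symptoms, recovery measures and satisfaction does not isolate satisfaction and gives no direction, size or interval for it.
- *Statistical Analysis section.* Data are summarised by treatment group, and differences are summarised with Hedges *g* or odds ratios. That effect-size sentence directly follows a description of participants at study start, so its reach to satisfaction is unclear. Even if it does apply, no interval and no handling of repeated ratings is stated.
- *The further analyses in the satisfaction paragraph.* These cover each visit, the course of the study and the end of the study, but no method is named.

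**3. Size.** The point disputes no number. The planned sample size, as background:

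- Inputs (Study Population and Sample Size; Randomization and Blinding): N = 130, 1:1, α = .05, power 0.80, *d* = 0.50. Two-sided testing is assumed.
- The two-sample *t* test needs 63.8, so 64 per arm and 128 in total. Power at 65 per arm is 0.808. The stated 130 is reproduced to within two participants.

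The 95% half-width for a standardised difference near zero is 1.96 × √(2/n per arm):

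- n = 65: 1.96 × √(2/65) = 0.344 SD.
- n = 49 (assumed 25% missing; 65 × 0.75 = 48.75): 1.96 × √(2/49) = 0.396 SD.

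With the *t* quantile the half-width is 0.35 SD at 65 per arm, and 0.39 and 0.42 SD at assumed sizes of 52 and 45. These figures are for a single-visit comparison. They show that an interval is feasible at this sample size, and that a gap in means of about a third of an SD would still be compatible with no difference.

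**The case against.** The strongest reply has four parts.

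- **This is a journal article.** Item-level modelling of a study-specific survey is commonly left to an SAP, which is not shown. That would dispose of a complaint about mere silence. The article is not silent, though: it states a method for this endpoint, and that method does not match the objective as worded. An SAP that follows the article would inherit the gap.
- **A descriptive summary can be legitimate.** Comparing two products does not require a hypothesis test, and the surveys are paired with qualitative interviews. This stands. It argues for an estimate with an interval rather than a test, or for wording the objective as descriptive.
- **Uncertainty is not wholly absent.** SDs with group sizes allow a rough interval at each visit. This is true, but readers would have to build it themselves, and it would not use the repeated ratings.
- **One model per survey item would multiply tests with no multiplicity rule.** This stands, and the fix is limited to one prespecified measure for that reason.

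A reader might infer something stronger: that the plan only tabulates satisfaction, produces no between-arm contrast at all, and so cannot say which product satisfies more. The article does not support that. The MANOVA includes satisfaction, the Hedges *g* and odds-ratio sentence may extend to it, and unnamed further analyses are promised. Nor should satisfaction be called the trial's subjective-engagement outcome without qualification. The abstract links subjective engagement to the surveys, but the Overview lists the two as separate items.

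**Conclusion.** The point holds in a limited form. The objective is comparative and longitudinal. The analysis stated for it is descriptive, and no satisfaction-specific between-arm estimate or confidence interval is named. The pooled MANOVA is the only stated inferential analysis that includes satisfaction, and it cannot fill that role.

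The half-widths of 0.34 to 0.40 SD are the generic precision of a two-arm comparison of this size. They do not measure an error in the plan. They assume equal arms of 65, or of 49 under an assumed 25% loss, and a difference near zero.

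The primary analysis is unaffected. The conclusion rests on the article alone; a fuller protocol or SAP may already name the contrast, in which case only the article's wording is at issue. The change is worth making because it is cheap and bears on a stated design aim of the product.

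**What to change.** In the satisfaction paragraph of the Secondary Endpoint Analysis section (and in the SAP):

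1. Prespecify one measure: a single satisfaction item or the mean of the post-baseline items.
2. Estimate the PEAR-008 versus reSET-O difference with a 95% CI, over weeks 4, 8 and 12 and at week 12.
3. Use the repeated-measures mixed model already planned for the other scales, or an ordinal equivalent if a single item is chosen (the effect is then an odds ratio). Include treatment, week, treatment × week and the stratification factors site and gender.
4. Report the contrast itself. The likelihood ratio test in the primary-endpoint approach drops treatment and its interaction with week together, so on its own it gives neither direction nor size.
5. Keep the remaining items and the visit-by-visit tables as descriptive support.

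If no comparison is intended, reword the Table 1 objective as descriptive instead.

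The cost is a wording change and one extra secondary analysis on data already being collected, with no added participant burden. The downside is one more secondary result, so it should be reported as an estimate with an interval and without a confirmatory claim.
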